
### Statistical considerations

#### Study design/endpoints

Single center, open-label proof-of-principle phase II trial to assess immune response and biomarkers potentially predictive of response. The primary objective of this study will be ***immunological efficacy***, as assessed by quantification of circulating immune effectors specific for a selected panel of tumor antigens. Secondary endpoints will be the predictive value of pretreatment serum biomarkers in identifying patients who are likely to benefit from high-dose IL-2-based therapy, toxicity, response rate (RR) and overall survival (OS). The analysis will be performed on an intention-to-treat population, *i.e.* all patients who have received at least one cycle of therapy. All time-dependent clinical endpoints (RR and OS) will be estimated with the Kaplan-Meier method. Frequency tables will be performed for all categorical variables. Continuous variables will be presented using mean and standard deviation or median and range.

Given the explorative intent of the study and the limited sample size, we are aware of being exposed to a high level of false-positive results. Unless otherwise indicated, analysis of demography and baseline characteristics will be performed on all enrolled patients. Demographic and laboratory results will be summarized using descriptive statistics. The percentage of patients reporting an adverse event (AE) up to 30 days after the end of HD-IL-2 treatment will be calculated with 95% confidence intervals by type of AE. The overall rate of grade 3–4 related AEs will be calculated. In addition, summary statistics of clinically significant laboratory abnormalities will be tabulated. The time of disease progression and the initiation of new therapies will also be documented.

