#### Method and timing

Response will be calculated according to irRC criteria. For the purposes of this study, after baseline tumor staging performed on the day before the first treatment cycle, patients will be re-evaluated for response every 8 weeks during therapy and every 12 weeks during follow up. Confirmatory scans will also be performed no less than 4 weeks following initial documentation of objective response and before discontinuation of treatment due to irPD.

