### Secondary clinical efficacy endpoints based on irRC

***Immune-related major durable disease control rate (irMDDCR)***: the proportion of treated subjects showing a disease control of 24 weeks measured from week 12, or from the date of the first overall response of irCR or irPR, until the date of irPD or death (whichever occurs first). For a subject who undergoes tumor resection following disease control but prior to disease progression, duration of disease control will be censored at the date of the last evaluable tumor assessment on or prior to the date of resection. Any subject who is unevaluable for MDDC for various reasons, *e.g.* censoring, lost to follow up, not assessable or unknown tumor assessments, will be considered a non-responder.***Immune-related objective response rate (irORR)***: the proportion of treated subjects with an immune-related best overall response (irBOR) of confirmed irCR or confirmed irPR.***Immune-related time to response (irTTR)***: the time from first dosing date until the measurement criteria (using irRC) are first met for overall response of irPR or irCR (whichever status comes first, and provided it is subsequently confirmed).***Immune-related duration of response (irDOR)***: the time between the date on which the measurement criteria (using irRC) are first met for an irCR or irPR (whichever status comes first and provided it is subsequently confirmed) and the date of irPD or death (whichever comes first). For a subject who undergoes tumor resection following response but prior to disease progression, irDOR will be censored on the date of the last evaluable TA or prior to the date of resection.For subjects who are still alive and have no progressive disease, as assessed by the investigator using irRC, irDOR will be censored on the date of the last evaluable tumor assessment.***Immune-related progression-free survival (irPFS)***: the time between the first dosing date and the date of irPD, or date of death, whichever occurs first (*i.e.* subjects who die without reported irPD will be considered to have progressed on the date of death). For subjects with no reported post-baseline tumor assessment, irPFS will be censored on the day of first dosing. For a subject who undergoes tumor resection following disease control but prior to disease progression, irPFS will be censored on the date of the last evaluable tumor assessment or prior to the date of resection. For subjects who are still alive and have no irPD, irPFS will be censored on the date of the last evaluable tumor assessment.***Overall survival (OS)***: the time from randomization until the date of death. For those subjects who are still alive, OS will be censored at the recorded last date of subject contact, and for subjects with a missing recorded last date of contact, OS will be censored at the last date the subject was known to be alive.***Immune-related time to progression (irTTP)***: the time from randomization to the first date of documented irPD (or death). Subjects without progression will be censored at their last tumor assessment date. Subjects without progression but who receive additional follow-up anticancer therapy will be censored on the date of their last tumor assessment prior to receiving the new therapy. Subjects with progression following additional anticancer therapy will also be censored on the date of their last assessment prior to receiving the therapy.***Death on study***: any death occurring between the date of randomisation and up to 30 days after the end of treatment must be reported to the Coordinating Center within 24 hours as a serious adverse event (SAE), regardless of the relation to study drug(s). Deaths occurring during the study follow-up period (*i.e.* more than 30 days after the last vaccine dose) need only to be reported as an SAE if it is thought that there is a possible correlation with the study treatment(s). All deaths must be reported on the Death Report section of the CRF regardless of cause.

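### Response rate is defined as a proportion of treated patients but assigned to Kaplan-Meier, which would overstate it if patients who fail without responding are censored before later responses

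*Protocol article*

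**What the plan says.** In the protocol article, Study design/endpoints lists response rate (RR) among the secondary endpoints and then fixes the estimator: "All time-dependent clinical endpoints (RR and OS) will be estimated with the Kaplan-Meier method". The analysis population there is "all patients who have received at least one cycle of therapy". The same paragraph adds: "Frequency tables will be performed for all categorical variables".

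Secondary clinical efficacy endpoints based on irRC defines irORR as "the proportion of treated subjects with an immune-related best overall response (irBOR) of confirmed irCR or confirmed irPR". The timing of response is a separate endpoint, irTTR: "the time from first dosing date until the measurement criteria (using irRC) are first met for overall response of irPR or irCR". Duration of response (irDOR) also has its own definition. Censoring rules are written for irDOR, irPFS, OS and irTTP, but none for irORR or irTTR. For disease control (irMDDCR), also a proportion, a patient who cannot be evaluated "will be considered a non-responder".

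**The concern.** The two sections cannot both be followed. A proportion of treated patients has no time origin and no risk set, so calling it time-dependent and estimating it by Kaplan-Meier changes what is being estimated.

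The practical worry is bias in one direction. Kaplan-Meier applied to time to response needs some handling of patients who fail without responding. The usual handling is to censor them, which assumes that they would go on to respond at the same rate as those still under observation. Death, or confirmed irPD with treatment stopped, is a competing event, and that assumption is then wrong. The result estimates a response rate in a hypothetical setting without failures, not the proportion that the article defines.

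The article's background gives 15% to 17% objective response for high-dose IL-2, and readers are likely to set this trial's figure beside it. A figure raised by the estimator alone could look like a gain from adding radiotherapy.

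**Working it through.** **The plan's own figures.** The article gives no figure for the clinical response rate. Its only computed design is the two-stage rule for immune response (go on with at least 3/7, active with at least 11/19, 40% against 70%). That rule reproduces. Summing, over x = 3 to 7, P(X = x; 7, p) × P(Y ≥ 11 − x; 12, p) gives 0.0841 at p = 0.40 and 0.9028 at p = 0.70, within the stated errors of 0.10. It does not use RR.

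**Inputs.** From the article: 19 patients; about 16% response to IL-2 in melanoma (Background); and the scan schedule, "patients will be re-evaluated for response every 8 weeks during therapy and every 12 weeks during follow up". Assumed, because the article gives neither: when responses occur, and how many non-responders fail between scans.

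**Direction.** Let d_k be the responses at scan k, n_k the number at risk, and S_k the Kaplan-Meier probability of no response after scan k.

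- 1-KM = 1 − Π(1 − d_k/n_k).
- Equivalently, each response at scan k adds S_(k−1)/n_k.
- With no earlier censoring that weight is 1/19, and the total is the plain proportion.
- Each censoring lowers n_k without lowering S, so every later response weighs more than 1/19.

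Hence 1-KM is never below the proportion, and exceeds it as soon as a response follows a censoring.

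**Worked case (assumed counts).** There are 3 responders, one per scan, with 8 non-responders censored after scan 1 and 5 after scan 2.

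| Scan | At risk | Responses | Censored afterwards | Weight of the response |
|---|---|---|---|---|
| 1 | 19 | 1 | 8 | 1/19 = 0.053 |
| 2 | 10 | 1 | 5 | (18/19)/10 = 0.095 |
| 3 | 4 | 1 | 0 | (18/19)(9/10)/4 = 0.213 |

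1-KM = 1 − (18/19)(9/10)(3/4) = 0.361, against 3/19 = 0.158.

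The same three responders under other assumed patterns:

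- 2 then 1 responses, with 6 censored between them: 1 − (17/19)(10/11) = 18.7%.
- 1, 1, 1 responses, with 6 then 5 censored between them: 1 − (18/19)(11/12)(5/6) = 27.6%.
- All three at the first scan: 3/19 = 15.8%.
- Failures kept in the risk set to the end: 1 − (18/19)(17/18)(16/17) = 3/19 = 15.8%.

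**Average size.** Take a true rate of 16% and three scans. Responders fall at scans 1, 2, 3 with shares t_1, t_2, t_3. A fraction c of the remaining non-responders is censored after each scan. The expected share of patients at risk at scan k is 0.16(t_k + … + t_3) + 0.84(1 − c)^(k−1), and the expected share responding is 0.16 t_k.

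For equal timing and c = 0.35:

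- The shares at risk are 1, 0.107 + 0.546 = 0.653, and 0.053 + 0.355 = 0.408.
- 1-KM = 1 − (1 − 0.0533/1)(1 − 0.0533/0.653)(1 − 0.0533/0.408) = 0.244.

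Simulated trials of 19 patients agree with this formula to the nearest percentage point:

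| Timing of responses over the 3 scans | c = 20% | c = 35% | c = 50% |
|---|---|---|---|
| Equal | 20% | 24% | 32% |
| 60/30/10 | 18% | 20% | 24% |
| 80/15/5 | 17% | 18% | 20% |
| All at scan 1 | 16% | 16% | 16% |

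**Exact interval for the proposed estimator.** Clopper-Pearson for 3/19 runs from the 2.5% point of Beta(3, 17) to the 97.5% point of Beta(4, 16): 3.4% to 39.6%.

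**The case against.** The best defence is that the sentence is loose drafting in a condensed article. The irORR definition already fixes numerator and denominator, best overall response is categorical, and frequency tables are promised for categorical variables, so the plain proportion could be reported under the existing text. That is plausible, but the sentence names RR expressly. RR cannot be read as shorthand for time to response or duration of response, because irTTR and irDOR are defined separately. The conflict stays.

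Three further objections limit the point, and they stand.

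- A reader might infer that the planned estimate is bound to be too high. The article does not support that: it gives no censoring rule for RR, and if failures stay in the risk set, or all responses come before any censoring, 1-KM equals the proportion.
- A reader might infer that a patient who progresses can no longer respond. Under the irRC rules in the article, progression needs confirmation at two consecutive timepoints, and a confirmatory scan is required before stopping for irPD. Response after a first, unconfirmed progression is therefore possible. The competing-event argument holds strictly for death, and in practice for confirmed irPD with discontinuation.
- RR carries no test, threshold or planned historical comparison, and the article itself warns of a high level of false-positive results. With 3.4% to 39.6% around 3/19, even the correct proportion could not establish a benefit of radiotherapy.

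**Conclusion.** The stated estimator is wrong for the endpoint as the article defines it, and the two sections must be brought into line. That conclusion rests on the text alone.

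The upward bias is conditional: it needs non-responders who die or have confirmed irPD to be censored, and at least one later response. Its size cannot be fixed from the article. Under the assumptions shown, a true 16% becomes anything from 16% (all responses at the first scan) to about 32% on average (equal timing, half of the remaining non-responders censored per scan). The 36% case shows what is possible in a single trial, not what to expect.

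It would go too far to conclude that the trial's main result is at risk. The go/no-go rule uses immune response only (3/7 and 11/19), and its error rates reproduce. This is a should-fix matter for a secondary endpoint.

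**What to change.** Remove RR from the Kaplan-Meier sentence in Study design/endpoints and state in its place:

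- irORR is the number of patients with confirmed irCR or irPR divided by all treated patients, with an exact (Clopper-Pearson) 95% confidence interval.
- Patients who cannot be evaluated count as non-responders, extending to irORR the rule already written for irMDDCR.
- Kaplan-Meier is used for OS, irPFS and irDOR.
- If the timing of response is of interest, it is described by a cumulative incidence function with death or confirmed irPD as the competing event.

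The cost is a few lines of text. No extra patients, visits or data are needed, and the two-stage design does not change.

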### Sample size/accrual rate

This is a proof-of-principle trial with a minimax two-stage design:Step 1: 7 patients enrolled. A 40% immune response will preclude further study, whereas a 70% response rate will indicate that further study is warranted. Using alfa and beta errors of 0.10, if an immune response is observed in at least 3 of the 7 patients enrolled during the first stage, the study will go on with:Step 2: recruitment of 12 additional patients.

Treatments will be considered active if an immune response is observed in 11 out of 19 patients treated. An enrolment period of 20 months is planned, with an accrual rate of about 1 patient per month. There are no patient stratification factors planned.

### Study approval

The protocol, informed consent and any accompanying material provided to the patient were submitted by the investigator to the Local Ethics Committee for review. Approval from the Committee was obtained before starting the study (EudraCT no. 2012-001786- 32).

## Discussion

The development of target agents to treat melanoma and renal cell carcinoma has partially changed the history of patients with advanced disease. VEGF axis inhibitors have almost doubled the survival (from 12 to 22 months) of advanced RCC patients [46], as have BRAF inhibitors for advanced melanoma patients in a second-line setting [47]. However, these targeted agents rarely induce a complete and durable response. In contrast, HD-IL-2 has been shown to elicit durable responses ranging from 10% to 15% in melanoma patients and from 15% to 25% in those with RCC. Standard HD-IL-2 administration requires hospitalization and a dedicated team to monitor for capillary leak syndrome. Although patients often usually develop a flu-like syndrome and severe fatigue, these side-effects resolve after suspending the infusion, without sequelae. Toxicity from TKI or mTOR inhibitors for RCC and from chemotherapy, BRAF inhibitors or anti-CTLA-4 antibodies for melanoma are low-grade but continuous and exert a negative impact on quality of life. Furthermore, some toxicities have an initially mild clinical presentation and can, if not recognized, rapidly become severe and potentially life-threatening events [46,48-50]. If HD-IL-2 is to remain a component of a curative treatment strategy in patients with metastatic melanoma or RCC [51], its therapeutic index must be improved. Two current areas of research into immunotherapy are the elimination of immune suppression and the improvement of patient selection. Based on our understanding of mechanisms of action, some biomarkers of response to IL-2 could help to identify a subset of patients who would probably benefit from treatment.

Up to now, the majority of putative predictors of IL-2 response have been post-treatment variables, such as the height of rebound lymphocytosis, treatment induced thrombocytopenia, the development of autoimmune thyroiditis and vitiligo, and the decrease in the absolute number and frequency of peripheral Tregs. In RCC, the level of carboxic anhydrase IX in primary tumors has been found to be a potentially useful pretreatment predictor. In both melanoma and RCC, (high levels of) serum vascular endothelium growth factor (VEGF) and fibronectin have also been identified as independent predictors of non-response and poorer overall survival. Other analyses of pretreatment factors have correlated IL-2 with the Cw7 phenotype and low serum levels of IL-6 and C-reactive protein, but none have proven to be sufficiently predictive of clinical benefit to be useful in selecting candidates for IL-2 therapy [43,44].

## Conclusions

As long as HD-IL-2 remains a necessary component of a curative treatment strategy in patients with metastatic melanoma or RCC, we must strive to improve its therapeutic index. Two current areas of investigation into immunotherapy focus on the elimination of immune suppression/regulation and the improvement in patient selection. Based on our understanding of the mechanisms of action, biomarkers of response to IL-2 might allow us to accurately select a subset of patients who will benefit from treatment. The main aims of this study are to improve patient selection and reduce toxicity, whilst also guaranteeing the same clinical benefit. In an attempt to develop a more manageable and better tolerated therapeutic schedule it has been decided to try a short IL-2 infusion repeated every 21 days, to add corticosteroids [38] to reduce the risk of capillary leak syndrome, and to add radiotherapy to exploit the abscopal effect [52,53].
